### Study population and recruitment

Eligible women with two or more unexplained pregnancy losses, will be included during a visit at the RPL clinic at MUMC+ or first trimester pregnancy clinic at the RUMC. These women are mostly referred by their general practitioner or other regional clinics in the southern or eastern part of the Netherlands. A pregnancy prior to a pregnancy loss, must be confirmed at least by either serum or urine beta-human chorionic gonadotropin, as ectopic and molar pregnancies are excluded in this definition. According to current (inter)national guidelines, the clinical work-up of women with RPL includes; a standardized history from the couple, maternal screening for antiphospholipid antibodies (anticardiolipin, lupus anticoagulant and β2 glycoprotein I), maternal thyroid screening, assessment of anatomical uterine anomalies, paternal screening for sperm DNA fragmentation, and parental karyotyping if indicated (1). Only women with unexplained RPL, not aiming to conceive within the study time frame of 3 to 4 months are eligible to participate. Furthermore, to ensure that there is no influence of a recent pregnancy loss or birth, women should be at least 2–3 months after their last pregnancy loss or birth. Further exclusion criteria are age above 40 years, body mass index above 40, current use of immune suppressive medication or hormonal contraceptives, current infection with the human immunodeficiency virus or symptomatic genital infections such as chlamydia or gonorrhea, pre-existent diabetes mellitus, autoimmune disease or overt cardiovascular disease, and vaccination 1 month prior to or during sampling and intervention.

On average, 30 new couples who experienced RPL visit our clinic every month, of which approximately 15 women have unexplained RPL. These women will be informed about the study by the health professionals in our clinic and a patient information folder will be handed out to women who are interested to read about the study in more detail. The health professional also asks for permission to pass their contact information to the study investigator. Within 1 week women will be contacted by the study investigator to get additional verbal information about the study and answer possible questions. During this consultation, the study investigator will ensure that all subjects will be given full and adequate verbal and written information about the nature, purpose, possible burdens and benefits of the study. Furthermore, it will be emphasized that participants are free to withdraw from the study at any time without specific reason. After eligibility is verified, women are free to take the time they need before deciding if they would like to participate or not. We estimate that monthly approximately 4 out of these 15 eligible women would like to participate in the intervention study. Additionally, we anticipate extra participants via RiNet (Reproductive Immunology network in the Netherlands)^1^ and via Freya (Dutch association for women with fertility problems).^2^ Information about the study and contact details will be provided on both websites. In this way, women who are interested in possible participation can contact the study investigator directly. Further course will be the same as for women who are informed about the study in the RPL clinic at MUMC+ or first trimester pregnancy clinic at the RUMC.

In our clinical experience we observed profound willingness in this specific patient group to participate in scientific studies which potentially help them and future patients. Our inclusion rate is however anticipated on the more modest side, because we do respect practical concerns, mainly related to time investment issues in couples who would like to conceive on short notice.

A total of 30 women with unexplained RPL will be included in this study to participate in the intervention group, additionally a maximum of 30 RPL women will be included under similar criteria in the timeline control group. Allocation was non-randomized as patients were allocated based on what was considered most appropriate for their individual circumstances.

### Study procedures and data collection

In short, a questionnaire on baseline characteristics and on baseline exercise levels will be conducted before intervention. For immunological assessment, menstrual blood will be sampled before, during, and after intervention. Peripheral blood and a vaginal swab will be sampled before and after intervention. For assessment of the cardiovascular system, a transvaginal ultrasound examination of both uterine arteries will be performed before intervention. Hemodynamic responses during a tilt test and maximal oxygen consumption during a VO_2_max test will be measured both before and after intervention. For metabolic assessment, measurements of metabolic components in peripheral blood and urine plus body characteristics will be determined before and after intervention. The intervention consists of 12-weeks moderate training. One year after intervention women will receive a final short questionnaire regarding pregnancy outcome.

#### Questionnaires

Before the intervention women will receive two questionnaires; one for assessing baseline characteristics such as age, medication use, information on gynecological history and obstetric history and one for standardized assessing baseline exercise levels. A year after completion of the intervention, women will receive a short digital questionnaire with questions about subsequent pregnancy outcome.

#### Immune assessment

•Menstrual blood and peripheral blood

Peripheral blood will be collected during a visit to the RUMC or MUMC+. Menstrual blood will be self-collected by the subject during 4 cycles before (T0), during (T1: week 4 in intervention, T2: week 8 in intervention) and after the intervention (T3). Women will receive verbal and written instructions on how to collect menstrual blood. Each cycle menstrual blood will be collected in 3 blocks of 12 h (total of 36 h) by use of a menstrual cup. A menstrual cup is a small silicon cup that can be used similarly like a tampon. All materials necessary to collect menstrual blood, including one menstrual cup since this cup can be re-used, will be send to the participant by postal service. When collection of the samples is completed, the material will be delivered in the hospital or sent to the lab directly by postal service. Our study group has gained experience with this protocol in previous studies (9, 18).

Peripheral blood mononuclear cells (PBMC) and menstrual mononuclear cells (MMC) will be isolated from the peripheral and menstrual blood by density gradient centrifugation. Number, phenotype, and function of these cells will be studied using flow cytometry. In short, NK cell receptors related to activation, inhibition, and memory function, will be analyzed. Functionality of NK cells will be determined by measuring the intracellular production of cytokines. Furthermore, cytotoxic potential of NK cells will be investigated by culturing NK cells with K562 target cells and degranulation potential will be assessed by CD107 expression and cytokine analysis such as IFN-γ production of different NK cell subsets. Additionally, menstrual mononuclear cells will be used for metabolomic analyses, targeting several lipids including glycerophospholipid and sphingolipid metabolism and microbiome related metabolites.

•Vaginal swab

Vaginal swabs for microbiome analyses will be collected with Copan flocked swabs and placed in eNAT buffer and stored at −20°C. DNA extraction of the vaginal swabs will be performed using a buccal swab extraction kit. Briefly, collected swabs samples will be thawed, vortexed and incubated with lysis buffer, proteinase K and elution buffer. For interspace profiling, amplification of the intergenic spaces (IS) regions will be performed with the IS-pro assay. IS-pro is a eubacterial technique based on the detection and categorisation of the length of the 16S-23S rRNA gene IS region, as the length of this IS region is specific for each bacterial species. Phylum-specific fluorescently labeled PCR primers will be used for taxonomic classification.

#### Cardiovascular assessment

•Transvaginal ultrasound

To evaluate blood flow to the uterus, the resistive index (RI) and pulsatility index (PI) of both uterine arteries will be examined by transvaginal route. After obtaining a sagittal image of the uterus, cervical canal and detection of the internal ostium, the uterine artery will be identified via color flow mapping and will be measured by pulsed-wave Doppler flow velocity waveforms of the ascending branch of both uterine arteries.

•Hemodynamic responses during tilt test

A tilt test will be performed under standardized environmental conditions by an experienced researcher. During the tilt test a woman first remains supine for 20 min, after which her body posture will passively be changed from 20° head-down tilt (−20°) to 60° head-up tilt (+60°), in steps of 20° at 8-min intervals. Heartrate and arterial blood pressure will be measured continuously using a monitoring device, called a Finometer, attached to a finger. The activity of the sympathetic nervous system will be derived by means of an arithmetic processing of the beat-to-beat changes in heartrate and blood pressure over time (47).

•VO_2_max test

Physical fitness will be determined as the peak oxygen uptake (VO_2_max: milliliter minute^–1^ kilogram^–1^) during a maximal cycling test on a cycle ergometer. The VO_2_max test will be performed under standardized environmental conditions and by an experienced researcher. During the test several parameters will be measured continuously. These non-invasive measurements include breath oxygen uptake by means of analysis of inhalation (O_2_ input) of and exhalation (CO_2_ output) and heartrate plus rhythm by electrocardiogram. The VO_2_max test will endure cycling in total for 10 to 30 min, with every minute an increase of 10 watts until total exhaustion.

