### Sample size

The effect of this interventional cohort study on CD56^bright^ eNK cells is hard to predict due to the novelty of this study using uterine NK cells as our primary objective. As for peripheral NK cells, a large meta-analysis showed an overall striking increase in cell count during moderate exercise training (186–344% of initial resting counts) (44). Since it is believed that training evokes redistribution of cells between blood and tissues due to increased hemodynamics (47), we hypothesize that moderate exercise possibly enables mobilization of NK cells to the endometrium and therefore affects CD56^bright^ eNK cell numbers. Moreover, after moderate exercise training, numbers of peripheral NK cells overall decreased to their initial NK cell count along with an analogous depression of cytolytic activity before complete recovery (44). Although at first these changes per training seem unlikely to have a major influence on general population health, it could be that a cumulative period of immune depression becomes of greater importance, especially to reproductive health. As these studies from this meta-analysis included around 20 subjects to show an effect on peripheral NK cells, we will aim to end up with around 20 women for data analysis. Furthermore, based on previous research showing discriminatory levels of the peripheral NK cell marker LILRB1 in two independent studygroups (8) we expect a detectable significant difference for a mean fluorescent intensity of 473 between group 1 (mean 771 ± 600) and group 2 (mean 298). When comparing two independent study groups for a continuous endpoint with an alpha of 0.05 and a beta of 0.2, a total number of 50 women, 25 in each group is needed to detect this difference of 600 and show discriminatory levels of NK cell markers. Additionally, we performed a pilot study to evaluate the feasibility of training women with RPL, to determine the modifiability of risk factors for RPL (evaluations of CD56^bright^ eNK cells were not part of this pilot study). We found that already after 1 month of supervised training, 9 out of 12 women significantly showed an improved VO_2_max (26.7 versus 27.4, *p* = 0.024) and one woman was unable to complete her trainings (unpublished data). Therefore, we expect that after a longer period of physical training at least 75% of the included women will improve their physical fitness (48).

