#### Metabolic assessment

•Peripheral blood and urine

Collection of peripheral blood will be done during a visit to the RUMC or MUMC+ at a similar timepoint as for the immune assessment so that women need to donate blood only once. A first-morning urine sample will be self-collected. Blood and urine samples will be sent to the central diagnostics laboratory of the RUMC or MUMC+ for standardized assessment of metabolic components such as triglycerides and cholesterol levels, glucose, insulin, and creatinine.

•Body characteristics

Measurements of body characteristics such as weight, height and waist-hip circumference will be performed.

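### Fitness is defined only as peak VO2 per kilogram, so weight lost during training would read as a fitness gain; absolute VO2 should be analysed beside it

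*Protocol article*

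**What the plan says.** Under Cardiovascular assessment the article says "Physical fitness will be determined as the peak oxygen uptake" and gives the unit as millilitres per minute per kilogram. The value comes from a cycle test "with every minute an increase of 10 watts until total exhaustion". The signals recorded include "breath oxygen uptake by means of analysis of inhalation" and exhaled air, with heart rate by electrocardiogram. On conduct it adds: "The VO_2_max test will be performed under standardized environmental conditions and by an experienced researcher".

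Under Metabolic assessment, "Measurements of body characteristics such as weight, height and waist-hip circumference will be performed". Study procedures and data collection confirms the timing: metabolic components "plus body characteristics will be determined before and after intervention".

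Physical fitness measured by maximal oxygen consumption is one of the secondary objectives. Under Statistical analysis, values are compared before and after by a paired t-test or Wilcoxon test, and between the intervention and time control groups by a t-test or Mann-Whitney test.

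The Sample size section reports from the pilot that "9 out of 12 women significantly showed an improved VO_2_max (26.7 versus 27.4", followed by p = 0.024, and concludes: "we expect that after a longer period of physical training at least 75% of the included women will improve their physical fitness".

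**The concern.** A per-kilogram value is a ratio, and training can move either part of it. The intervention adds two to three hours of cycling a week for 12 weeks, and women with a body mass index up to 40 are eligible, so some weight loss is plausible. A lighter woman with the same oxygen uptake scores higher. If the trained group loses weight, the trial could report better fitness when the change lies in the denominator.

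The control group does not solve this. Weight loss caused by training occurs in the trained group and so remains in the between-group difference. The same weight change also belongs to the metabolic assessment, so part of any association between change in VO2max per kilogram and change in weight-related metabolic measures would be arithmetic.

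The pilot sentence is a second, smaller matter. It presents a result that appears to concern the group mean as if it were a finding about individual women, and the expected share of improvers follows from it.

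**Working it through.** **Inputs from the article.** Pilot VO2max 26.7 before and 27.4 after one month, p = 0.024, 9 of 12 women improved (Sample size). Unit mL/min/kg (Cardiovascular assessment).

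**Assumed.** Body weights of 60 to 90 kg; the article gives none. A single typical woman stands in for the group means.

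**1. The plan's own figure.** 9/12 = 75%, which reproduces the expected share.

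**2. Size of the pilot gain.** 27.4 − 26.7 = 0.7 mL/min/kg, and 0.7/26.7 = 2.6%.

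**3. Weight loss giving the same rise.** Per-kilogram VO2 = absolute VO2 / weight. If absolute VO2 is unchanged, the after/before ratio equals W0/W1. Setting W0/W1 = 27.4/26.7 gives a loss of W0 × (1 − 26.7/27.4) = 0.0255 × W0.

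| Assumed weight | Loss matching the pilot gain |
|---|---|
| 60 kg | 1.5 kg |
| 70 kg | 1.8 kg |
| 80 kg | 2.0 kg |
| 90 kg | 2.3 kg |

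Check at 70 kg: 26.7 × 70 = 1869 mL/min, and 1869/68.2 = 27.4 mL/min/kg. Oxygen uptake has not changed.

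**4. Smaller losses.** At 70 kg, a loss of 1 kg raises the value by 26.7 × (70/69 − 1) = 0.39 mL/min/kg. A loss of 2 kg raises it by 26.7 × (70/68 − 1) = 0.79.

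**5. Effect on the planned tests.** Before-after: the shift in steps 3 and 4 is part of the paired difference. Between groups: the contrast is trained change minus control change. Retest learning cancels if it is alike in both groups. Weight loss caused by training does not cancel.

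**6. What the pilot p value describes.** Assume a two-sided paired t-test on 12 women. Then p = 0.024 corresponds to t = 2.616 on 11 degrees of freedom, so SE = 0.7/2.616 = 0.268, SD of change = 0.268 × √12 = 0.93, and the 95% CI is 0.11 to 1.29. A normal distribution with that mean and SD has 77% of women rising, close to 9 of 12. The p value therefore fits a test of the mean change.

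The count alone gives something else. If a rise and a fall were equally likely, P(9 or more of 12) = (220 + 66 + 12 + 1)/4096 = 0.073 one-sided, 0.146 two-sided. If the one woman who did not finish had no second test, P(9 or more of 11) = 0.033 one-sided, 0.065 two-sided. Neither gives 0.024.

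**The case against.** A reader might infer that any rise will count as improved, so that test noise will be reported as a training response. The documents do not support that. No responder endpoint or responder analysis is stated; improvement appears only as a pilot result and an expectation in the sample-size rationale. The planned tests use values. Symmetric noise does not shift a mean, so the paired test keeps its error rate against noise alone.

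A reader might also infer that greater effort at the second test will pass unnoticed, since the test runs to exhaustion and the article states no criterion for maximal effort. Such criteria, like a test-retest threshold, are details an article commonly leaves to the full protocol. The weekly calls are described as supporting completion of the training, not performance in the test. Differential effort in a non-randomised comparison remains possible, but its absence from the article is not an error.

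Other points against the concern are fair. Participants are asked to keep their diet unchanged, which limits weight loss without excluding it. The 0.7 gain is a one-month figure and the trial runs 12 weeks, so step 3 gives a scale and not a prediction. VO2max is not the only physiological measure, since tilt-test and metabolic data are also collected. Adjustment for BMI is planned, but the Statistical analysis section attaches it to the regression on interrelationships, not to the paired or between-group tests.

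What remains is that the only stated definition of fitness is per kilogram, and the planned comparisons do not tell weight loss from oxygen uptake.

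**Conclusion.** The point holds in limited form. Fitness as defined can rise through weight loss alone, and a loss of about 1.5 to 2.3 kg (assumed weights 60 to 90 kg) would match the whole one-month pilot gain. How much weight the women will lose is not known from the article, nor is the expected 12-week gain, so the size of any distortion in this trial cannot be stated.

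The pilot wording needs correction: p = 0.024 fits the mean change and not the count of 9 of 12, and a count from 12 women does not establish a response rate of 75%.

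The issue is minor. It touches one secondary outcome and the wording of the sample-size rationale, and leaves the primary eNK-cell objective unaffected.

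**What to change.** 1. Analyse absolute VO2max (L/min) beside the per-kilogram value, by the same paired and between-group tests. Interpret a per-kilogram rise as a gain in fitness only if absolute VO2 also rises.
2. As supporting description, report peak heart rate and peak respiratory exchange ratio (CO2 output over O2 uptake) at both tests.
3. In the Sample size section, restate the pilot as a mean change from 26.7 to 27.4 (p = 0.024), with 9 of 12 women showing an increase, after confirming that the nine were counted that way. Do not present 75% as an established response rate.

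The cost is wording and one extra analysis. Oxygen uptake, CO2 output, heart rate and body weight are already recorded before and after the intervention, so no visit, procedure or extra participant is needed.

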#### Metabolic assessment

•Peripheral blood and urine

Collection of peripheral blood will be done during a visit to the RUMC or MUMC+ at a similar timepoint as for the immune assessment so that women need to donate blood only once. A first-morning urine sample will be self-collected. Blood and urine samples will be sent to the central diagnostics laboratory of the RUMC or MUMC+ for standardized assessment of metabolic components such as triglycerides and cholesterol levels, glucose, insulin, and creatinine.

•Body characteristics

Measurements of body characteristics such as weight, height and waist-hip circumference will be performed.

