The intervention consists of a personalized 12-week heartrate-controlled cycle training program, that must be carried out on top of a subjects regular exercise regime and diet. Heart rate will be monitored by a Polar H10 heartrate monitor chest strap during cycle trainings. If women don’t want to participate in the training intervention, they will be asked to participate in a timeline-control group in which they receive similar questionnaires and assessments of their immune, cardiovascular and metabolic system. However, instead of an additional cycle training program of 12-weeks, they only follow their regular exercise regime and diet during an identical period. In this latter group, women will be included under similar criteria as the intervention group, preferably in a 1:1 ratio. Comparability between groups will be assessed on baseline characteristics prior to the intervention.

For both the intervention and control group, women will be asked to additionally donate menstrual blood at 4 and 8 weeks during the 12-week interval in order to assess intra menstrual cycle variation of eNK cells. Subsequently, all women will receive an identical immune, cardiovascular and metabolic assessment after 12 weeks and 1 year after intervention, a short questionnaire for monitoring subsequent pregnancy outcomes. See Figure 1 for a schematic overview of study design.

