### Statistical analysis

Normality of data will be evaluated with Kolmogorov-Smirnov tests or visual inspection of histograms. Descriptive data will be expressed as mean ± standard deviation for parametric continuous variables or as median and interquartile range for non-parametric continuous parameters or percentage for categorical variables. To test individual effects of our exercise intervention, parameters of the immune, metabolic, or cardiovascular assessments respectively, will be compared before versus after intervention, for which data will be assessed by parametric paired T-tests or non-parametric Wilcoxon signed rank tests. Moreover, to test group effects of our exercise intervention, parameters of the respective systems will be compared between the intervention and the time control group, for which data will be compared by parametric T-tests or non-parametric Mann Whitney U tests. Since we assume that the different systems might influence each other in the occurrence of recurrent pregnancy loss, correlation analyses will be used to examine interrelationships, specifically correlating changes of NK cell phenotypes with metabolic and cardiovascular parameters. Correlations between immune, metabolic and cardiovascular data will be assessed by univariate and multivariate logistic regression analysisand calculated as crude and adjusted odds ratios to correct for possible confounders such as BMI. Statistical significance will be defined as *P* < 0.05 using SPSS version 28.0.

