### Data management

Data will be collected in a single electronic cloud-based clinical data management platform; Castor EDC by the coordinating investigators of the RUMC and MUMC+. Furthermore, coordinating investigators will maintain adequate study records, including laboratory forms, signed informed consents, and will ensure that the subject’s anonymity will be guaranteed by confidentially coding patient data. In all documents, subjects will be identified by an identification code only and thus not by their names or any other feature by which subjects can be identified. The investigator will keep a separate Subject Identification Code List stored at the Department of Laboratory Medicine, Laboratory of Medical Immunology RUMC and Department of Transplantation Immunology MUMC+, which matches identifying codes with the subjects’ names. Therefore, only coded samples will be handled in the laboratory and the information is not directly traceable to the patient. The Code List will be maintained by the investigator in strict confidence. Access will be granted only to members of the research team if necessary, and to the study monitor if requested. Subject anonymity will be maintained throughout all archiving steps. All samples will be coded as followed: RUM-001 or MUM-001 dependent if sampling takes place in Nijmegen or Maastricht. All data will be handled confidentially.

All data will be stored and archived through the data management infrastructure of the institute, which will be kept for at least 15 years (following guidelines for minimal risk research Kwaliteitsborging Mensgebonden Onderzoek 2.0 + institutional DR policy). Materials will be stored for further investigation concerning this protocol with their corresponding code at −20°C, −80°C or within a liquid nitrogen storage for a maximum of 10 years. Following publication, raw and processed data will be archived for scientific integrity, which is only accessible upon request through the coordinating investigators and the researchers responsible for the data.

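### The secondary comparison of trained and control women is an unadjusted two-sample test across two hospitals; it can be biased by centre or laboratory differences if 12-week levels are compared and the centre mix differs between groups

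*Protocol article*

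**What the plan says.** All references are to the protocol article.

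- **Recruitment** (Study population and recruitment): women enter "during a visit at the RPL clinic at MUMC+ or first trimester pregnancy clinic at the RUMC", so each hospital recruits through a different type of clinic.
- **Laboratory** (Metabolic assessment): "Blood and urine samples will be sent to the central diagnostics laboratory of the RUMC or MUMC+ for standardized assessment of metabolic components". No single reading laboratory and no cross-calibration is described.
- **Group formation** (Study population and recruitment): "Allocation was non-randomized as patients were allocated based on what was considered most appropriate for their individual circumstances". The Study objectives and design section wants controls "preferably in a 1:1 ratio" and does not say that this holds within each hospital.
- **Group comparison** (Statistical analysis): "to test group effects of our exercise intervention, parameters of the respective systems will be compared between the intervention and the time control group". The tests named are the two-sample T-test and the Mann-Whitney U test. The section does not say whether the parameters are 12-week levels or changes from baseline, and centre is not mentioned.
- **Other analyses** (Statistical analysis): the before/after comparisons are paired. The cross-system analysis relates changes in NK phenotype to metabolic and cardiovascular parameters, with crude and adjusted odds ratios. BMI is given as an example of a confounder.
- **Centre is recorded** (Data management): samples are coded "RUM-001 or MUM-001 dependent if sampling takes place in Nijmegen or Maastricht".

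**The concern.** A two-sample T-test or Mann-Whitney test has no place for centre. The groups form by preference and circumstance, so the share of women from each hospital may differ between them. If the two hospitals also differ in laboratory calibration or in the women they recruit, that difference is carried into the comparison of levels and can look like a training effect or mask one.

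The comparison with controls is the part of the study that separates a training effect from a change over time. Comparing immunological effects with the control group is a listed secondary objective, and the Statistical analysis section extends the comparison to all three systems.

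**Working it through.** **1. The plan's own group size.** The Sample size section gives a difference of 473, an SD of 600, alpha 0.05 (taken as two-sided) and beta 0.2, and states 25 per group.

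n per group = 2 × (1.96 + 0.84)² × (600/473)² = 2 × 7.85 × 1.609 ≈ 25.3, or 26 rounded up. Power at 25 per group is 79.6% by the normal approximation. The stated figure is reproduced to within rounding. With 30 women included and about 15% drop-out, 30 × 0.85 = 25.5, which matches the planned number for analysis. This figure does not involve centre; it only sets the 25 per group used below.

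**2. Bias when levels are compared.** For a constant centre offset d (in SD units) and shares p₁ and p₀ of women from one hospital in the trained and control groups:

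bias = d × (p₁ − p₀)

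- 60/40 mix, d = 0.5: 0.5 × 0.20 = 0.10 SD
- 72/28 mix, d = 0.5: 0.5 × 0.44 = 0.22 SD
- 80/20 mix, d = 0.5: 0.5 × 0.60 = 0.30 SD
- equal mix: 0

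**3. False-positive rate of the unadjusted T-test on 12-week levels.** Simulation with no true effect, 25 per group, unit SD, nominal 5%, 20,000 runs per cell. Offsets and mixes are assumptions, because the article gives neither.

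| Centre mix, trained / control | 0.25 SD | 0.5 SD | 1.0 SD |
|---|---|---|---|
| 52% / 52% | 5.0% | 4.7% | 2.9% |
| 60% / 40% | 5.1% | 5.5% | 6.9% |
| 72% / 28% | 6.4% | 10.8% | 26.7% |
| 80% / 20% | 7.8% | 17.0% | 48.5% |

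With an equal mix the test becomes conservative, because the offset only adds variance.

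**4. Changes and paired tests.** In the same simulations (pre/post correlation assumed 0.5), the T-test on change scores and the paired test within the trained group stayed at about 5% in every cell. A constant offset cancels when each woman is measured by the same laboratory at both times.

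**5. Baseline adjustment without centre.** If the 12-week value is regressed on group and baseline with slope b, the bias left is (1 − b) × d × (p₁ − p₀). With b = 0.5, a 72/28 mix and d = 0.5, that is 0.5 × 0.22 = 0.11 SD. Baseline alone removes only part of the offset in a regression, so centre is needed as well.

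**6. Correlations between levels.** Two otherwise unrelated levels that are both shifted by d between equal-sized centres correlate at r = (d²/4)/(1 + d²/4). This gives 0.015 for d = 0.25, 0.059 for d = 0.5 and 0.20 for d = 1.0. It does not apply to NK changes, where a constant offset has already cancelled.

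**The case against.** The strongest case against is that the primary objective is a before/after change, analysed with paired tests, which a constant offset does not bias. The group comparison is secondary in a study that calls itself explorative. The article describes the metabolic assays as standardized and applies one set of eligibility criteria and one diagnostic work-up at both hospitals, so a large offset is not established. If changes are what will be compared, there is no inflation. The list of confounders for the cross-system models is open and could include centre. The full protocol and the statistical analysis plan are not shown. The metabolic markers are also measured at baseline in both groups, so an offset combined with an unequal mix would show there as a group difference.

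Most of this stands, and it limits the point. A reader might infer that centre differences necessarily distort the group comparison and all the cross-system correlations. The article does not support that. Bias requires both an unequal mix and a comparison of levels, and among the cross-system analyses only crude or level-based associations are clearly exposed.

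What remains is that the article does more than stay silent. It names an unadjusted two-sample test for non-randomised groups from two hospitals and leaves open whether levels or changes are tested. The planned check of baseline comparability names neither centre nor any action to take if the groups differ.

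**Conclusion.** The point holds for the secondary between-group comparison, conditionally. If 12-week levels are compared and the centre mix differs between groups, a centre or laboratory offset biases the result.

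The size cannot be derived from the article. On the assumed inputs, the false-positive rate is about 5% for an equal or 60/40 mix with an offset up to 0.5 SD. At 0.5 SD it is about 11% for 72/28 and 17% for 80/20. Offsets of 1.0 SD would be worse, but nothing in the article suggests that they are present.

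It would be wrong to infer that the primary analysis is compromised. The paired comparison is not biased by a constant offset, provided that each woman's samples go to the same laboratory at both times; the article implies this but does not state it.

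**What to change.** In the Statistical analysis section:

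- Replace the unadjusted between-group test with a regression of the 12-week value on group, baseline value and centre. Where a rank method is needed, use a van Elteren test on changes from baseline, stratified by centre. Either choice also settles whether levels or changes are analysed.
- Name centre alongside BMI among the confounders in the adjusted cross-system models.
- Report the group-by-centre counts, so that readers can see whether the mix differed.

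The cost is one or two degrees of freedom and a change of wording. No new data are needed, because the sample code already identifies the hospital and baseline values are collected in both groups.
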